## Abstract

**Background:**

Patients’ expectations toward any given treatment are highly important for the effectiveness of such treatment, as has been demonstrated for several disorders. In particular, in major depressive disorder (MDD), one of the most frequent and most serious mental disorders with severe consequences for the affected, the augmentation of available treatment options could mean a ground-breaking success. Repetitive transcranial magnetic stimulation (rTMS), a new, non-invasive, and well-tolerated intervention with proven effects in the treatment of MDD, appears particularly suitable in this context as it is assumed to exert its effect via structures implicated in networks relevant for both expectation and depression.

**Methods:**

All patients will receive rTMS according to its approval. Half of the patients will be randomized to a psychological intervention, which is a comprehensive medical consultation aiming to improve positive treatment expectations; the control group will receive a conventional informed consent discussion (in the sense of a treatment-as-usual condition). As outcome parameters, instruments for both self-assessment and external assessment of depression symptoms will be applied. Furthermore, psycho-immunological parameters such as inflammation markers and the cortisol awakening response in saliva will be investigated. Resting-state functional magnetic resonance imaging (rs fMRI) will be performed to analyze functional connectivity, including the cerebellum, and to identify neuronal predictors of expectation effects. In addition, possible cerebellar involvement will be assessed based on a cerebellar-dependent motor learning paradigm (i.e., eyeblink conditioning).

**Discussion:**

In this study, the effects of treatment expectations towards rTMS are investigated in patients with MDD. The aim of this study is to identify the mechanisms underlying the expectation effects and, beyond that, to expand the potential of non-invasive and well-tolerated treatments of MDD.

**Trial registration:**

German Registry of Clinical Studies (DRKS DRKS00028017. Registered on 2022/03/07. URL: https://www.drks.de/drks_web/.

## Introduction

### Background and rationale {6a}

Major depressive disorder (MDD) is one of the most frequent—and most serious—disorders with a lifetime prevalence of up to 20%. Besides cardiovascular diseases, it is the disease which causes the greatest individual suffering when regarding disability-adjusted life years (DALYs) and generates the highest public health costs in Western societies [1]. About one-third of patients meet the criteria for difficult-to-treat depression, also referred to as treatment-resistant depression [2], although the criteria applied here are sometimes inconsistent. In most cases, this refers to the group of patients who have not experienced a significant reduction of symptoms even after two attempts at drug therapy with sufficient dosage and treatment time. In view of this large number and the high level of suffering in depressive patients, there is an urgent need to improve the existing treatment options.

A new approach could be to influence a patient’s treatment expectations. This, of course, requires a deeper understanding of the underlying mechanisms. Expectations are essential for the success of a treatment, which was shown in the treatments of pain, anxiety, and Parkinson’s disease [3] in a study that found an overt treatment to be much more effective than a covert treatment which, due to its inherent concealment, renders smaller effects of expectation.

Expectations seem to play a major role in the treatment of MDD as there are pronounced placebo effects in studies regarding antidepressant medication [4]. Rutherford and colleagues [5] investigated overt vs. covert administration of citalopram and found that citalopram was only superior to placebo in cases of an overt treatment. Attempting to explain these effects, several studies argue that placebo and pharmacological effects cannot clearly be separated and that antidepressants exert their influence via interactions with the treatment context [6].

In MDD, in particular, a psychological intervention that was designed to enhance expectations was shown to improve the effect of antidepressant medication [7]. The intervention involved participants attending four weekly-held cognitive-psychoeducational group therapy sessions.

Today, the topic of treatment expectation may be of particularly great relevance, as patient-physician communication has taken a back seat in the clinical setting in the face of numerous bureaucratic and economic challenges. New insights into the impact of treatment expectations could drive significant change, for example, regarding the design of the patient education discussion.

Transcranial magnetic stimulation (TMS) therapy is approved for the treatment of depressed patients who did not sufficiently benefit from standard antidepressant pharmacotherapy; its effectiveness has been shown in several meta-analyses [8]. The stimulation site of TMS treatment is the left dorsolateral prefrontal cortex. It is usually applied for a duration of 4 to 8 weeks, 5 days a week for 30 min [8, 9]. To date, it remains unclear how exactly TMS exerts its effects. Resting-state (rs) functional imaging studies found characteristic alterations in MDD which can be influenced by TMS [10]. In MDD, a hyperconnectivity within the frontoparietal network (involving the dorsolateral prefrontal cortex and the posterior parietal cortex) and a hyperconnectivity within the default mode network (DMN, involving the prefrontal and cingulate cortex) have been reported [10]. After repetitive (r)TMS treatment, Philip and colleagues [11] found altered rs functional connectivity between the prefrontal cortex and the subgenual anterior cingulate cortex. Higher connectivity within the DMN seems to predict the beneficial effects of both pharmacotherapy and TMS.

Interestingly, these same networks are implicated in expectation effects: Burke and colleagues [12] conducted a meta-analysis on neuroimaging studies of placebo effects and compared clusters of activation (and deactivation) with TMS and deep brain stimulation (DBS) targets for depression treatment and found an extensive overlap. This raises both the question and the hypothesis: can we assume a bilateral interaction between placebo mechanisms and TMS?

Another interpretation of this observation could be that there seems to be an overlap of the underlying cognitive-affective and reward-based substrates in MDD and placebo effects [12].

The cerebellum has only recently been added as a part of the neural network underlying placebo effects [13]. Furthermore, newer studies suggest that the cerebellum is not only involved in the processing of sensory, but also reward predictions and prediction errors [14–16]. Several studies reported structural and functional alterations in the cerebellum in MDD [17], which could suggest pathophysiological involvement. Cerebellar dysfunction may contribute to abnormal expectation effects in MDD. Therefore, the cerebellum will be included in resting state network connectivity analyses. In addition, eyeblink conditioning will be performed, an associative learning paradigm that critically depends on the integrity of the cerebellum [16, 18].

In aiming to identify the different neurobiological players involved in expectations, relevant laboratory parameters should also be considered: numerous studies have demonstrated elevated inflammatory markers in unipolar depression, including CRP (C-reactive protein), IL-6 (interleukin-6), and TNFα (tumor necrosis factor α) [19]. These markers could objectify therapeutic success as an additional outcome parameter. Cortisol awakening response (CAR) is another biological marker altered in depressive disorder. In addition, CAR has been linked in brain imaging studies to networks that may also play a role in expectation effects (DMN, medial prefrontal cortex, and anterior cingulate gyrus) in such a way that it could be considered a predictor for expectation effects [20].

In summary, it is evident that patients’ expectations for a treatment represent a very important component of the placebo effect and are crucial for the response to the respective treatment [3, 21]. Expectations depend on various factors, such as personal experiences, the current situation including the context, individual attitudes, and available information [22, 23].

Not all of these factors can be influenced. Currently, it is unclear to what extent treatment expectations can be modified and how strong, and thus how relevant, such an effect could be. The study at hand aims to shed some light on this issue. Furthermore, the question arises whether the informed consent discussion could be a suitable starting point for influencing therapy expectations [24]. Should this prove to be the case, it would have promising and far-reaching implications for everyday doctor-patient communication.

TMS appears to be a particularly suitable form of treatment for investigating this matter, since placebo effects play a major role here, and moreover, the mode of action of TMS could be reinforcing precisely these results, i.e., amplifying expectancy effects.

Studies on the forms of treatment for depressive illness have in common that they show strong placebo effects, regardless of the form of treatment [25]. Expectations thus seem to play a particularly important role for the effectiveness of treatment in this disorder, not least because the impairment to develop hope and to expect something good to happen is a central symptom of this disorder. Therefore, both the disease and the form of treatment seem to be suitable for the research question of our study.

### Objectives {7}

The main objective of our study is to test the hypothesis that a higher expectation for the efficacy of TMS treatment leads to a better therapy success regarding the intensity of the depressive disorder. In this, we do not seek to investigate the efficacy of TMS in MDD per se, but rather the effects of treatment-related expectation. In order to realize this, the intervention as a more positive and comprehensive patient education aims to induce higher expectations, which, in the next step, is assumed to lead to a better outcome. Therapy success will be evaluated by means of psychometric tests and cognitive tasks. We further intend to explore a possible normalization of inflammatory parameters as an additional outcome parameter.

Furthermore, in an exploratory approach, the aim is to identify predictors of the expectancy effect in imaging, at the level of both biological and psychological parameters. Predictors of expectancy effects in functional connectivity in the rs activity in the DMN as well as in cognitive and emotional networks are to be identified. We also believe that CAR in saliva can be considered as a predictor of expectancy effects.

Another goal of our study is to investigate the role of the cerebellum in depression and expectancy effects: we hypothesize that mild cerebellar symptoms as well as a limitation in the acquisition of conditioned blink reflex responses (a cerebellum-dependent learning paradigm) can be detected in a subset of patients. Our hypothesis is that the expectancy effect is less pronounced in this group of patients, which is also reflected in the altered functional connectivity of the cerebellum.

### Trial design {8}

We are planning an interventional, monocentric, randomized, controlled trial with two MDD patient groups of 30 participants each.

Our study is of the parallel group type, i.e., we are looking at two groups of patients in parallel, with one group of patients receiving an intervention while the other one does not. The framework is “superiority”: we expect to see superiority in outcome parameters in the intervention group. The allocation ratio in the intervention versus the control group is 30:30.

As it is to be expected that about 10% of the data will be lost due to the complex study protocol with several examinations at a total of four time points, at least 35 patients should be recruited per group. This minimum recruitment number seems achievable based on our experience with previous studies. The details of the intervention are outlined below.

In addition, an age-, sex-, and education-matched control group of 30 participants will be recruited, who will serve as a control only for the additional experimental investigations, which is the MRI part and the eyeblink conditioning. In these two subprojects, the first step is to evaluate the changes in the context of depressive illness in general compared to a healthy control group, see the “Outcomes {12}” section.

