### Eligibility criteria {10}

Sixty patients with an MDD and 30 healthy, matched controls will be included in the study. Within the patient group, allocation to the intervention or control condition will be randomized and stratified for gender to ensure a balanced gender distribution.

The inclusion criteria are an age of 18–65 years, moderate to severe depressive episode (according to Hamilton Rating Scale for Depression, HDRS, as well as a structured clinical interview for DSM IV), and at least two different antidepressants without sufficient effect in the patient history.

The exclusion criteria include individuals under legal care and individuals in official or judicial custody, individuals with malignant diseases and/or in poor general condition, no sufficient hearing or reading ability, contraindications for TMS (that is, presence of ferromagnetic material, e.g., cochlear implants, pregnancy, cardiac pacemaker or epilepsy), previous TMS treatment, electroconvulsive therapy in the preceding 6 months, relevant structural lesions in MRI (apart from expected age-related changes such as mild cerebral microangiopathy in patients over 50 years of age or changes without expected relevance such as small arachnoid cyst), further relevant comorbidities such as substance abuse or dependence, organic mental disorders, dementia, or psychotic disorders.

In addition, the exclusion criteria relate to relevant comorbidities such as neurological disorders, e.g., multiple sclerosis, Parkinson’s syndrome, and cerebellar disease (excluding headache disorders), diseases that are associated with an inflammatory response and lead to permanently elevated inflammatory parameters and severe internal diseases that are accompanied by a significantly reduced general condition.

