#### Criteria for discontinuing or modifying allocated interventions {11b}

Overall, the study is at a very low risk for potential harm. No harm is expected from the intervention in the form of modified patient education about the approved therapy with TMS. Prior to the start of the study, study participants will be asked to indicate whether they would like to be informed of incidental findings in addition to this education.

The discontinuation criteria for individual participants are the occurrence of intolerable and/or unexpected undesirable side effects during the therapy with TMS, the occurrence of the exclusion criteria during the course of the therapy, violation of the study protocol, and other circumstances that would endanger the health of the participant if he or she continued to participate in the study, as well as on participant request. Change of medication during the treatment is not an exclusion criterion per se but will be recorded as an event that will need additional control.

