#### Relevant concomitant care permitted or prohibited during the trial {11d}

The aim is to ensure that during study participation, any existing drug and/or psychotherapeutic treatment is continued with as little change as possible. In the event of a relevant change during study participation, discontinuation must be discussed individually. Change of medication during the treatment is also not an exclusion criterion per se but will be recorded as an event that will need additional control.

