### Recruitment {15}

Through the newly established Center for Treatment-Resistant Depression (*Zentrum für Therapieresistente Depressionen*) at the LVR-University-Hospital Essen, a large number of interested and/or referred patients present themselves for a consultation. Furthermore, a flyer was created that summarizes the content of the study to be distributed to psychiatric practices. In addition, a training event on the topic of therapy-resistant depression will be conducted to familiarize potential referring physicians with the study. The recruitment of the healthy control group is based on age, gender, and education of the patient group. For this purpose, the study team recruits control subjects from the professional and private environments. In addition, an appeal via social media is planned in case not enough participants are found via the first step. The recruitment period is scheduled for a period of 1 year.

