#### Confidentiality {27}

All examination results are treated strictly confidentially. Person-identifying data (name, date of birth, contact details, written informed consent) are recorded in paper form. Furthermore, pre-existing conditions, previous treatments, and medications taken are recorded. Patients are asked for copies of out-of-pocket medical records if necessary. All person-identifying paper records are kept in a locked cabinet at the LVR-University-Hospital Essen. Only authorized members of the working group have access to the laboratory and the cabinets. The experimental data (questionnaires, computer-based test procedures, MRI data, sample IDs) are given a letter/number code, i.e., they are pseudonymized (procedure described above). The data are stored on a local PC, which is protected by a password. The pseudonymization list, via which an assignment of the number code to the person-identifying data is possible, is stored separately from the other documents in a lockable cabinet. All personal identifying data collected in the experiment, including the signed consent forms, will be kept until at least the end of the study and for a maximum of 10 years. Thereafter, all personal-identifying data, including the encryption list and the written informed consent form, will be destroyed. The remaining data is then stored permanently in anonymized form. Only the principal investigators and members of the working group have access to the local PC and the lockable cabinet. Pseudonymization means, as mentioned above, that name and date of birth are replaced by a code and their assignment to the individual participant is restricted to the staff members of this study. The participants are informed that the collected data will be published in pseudonymized (and in the course anonymized) form in scientific journals. They are also informed that pseudonymized or anonymized data can be made available to other scientists, e.g., by publishing such data on scientific data platforms or at the request of other scientists. The participants are informed about their rights according to the European Data Protection Regulation (EU-DSGVO), i.e., the right to information about the processing of their data, correction or deletion of their data, restriction of processing (only storage possible), objection to processing, data portability, revocation of their given consent with effect for the future, and complaint to the data protection supervisory authority. Participants are informed that they have a right to have their data deleted at request. They are also informed that data, once anonymized, can no longer be destroyed.

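### Healthy controls are matched only on age, sex and education while patients keep their existing drugs, so an eyeblink or connectivity difference credited to depression could partly be a medication effect

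*Protocol article*

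**What the plan says.** **Purpose of the comparison.** Trial design {8} adds a healthy group to the two randomised arms for the MRI and eyeblink subprojects, where "the first step is to evaluate the changes in the context of depressive illness in general compared to a healthy control group". Objectives {7} makes the cerebellum in depression a goal of its own: "we hypothesize that mild cerebellar symptoms as well as a limitation in the acquisition of conditioned blink reflex responses" will be found in some of the patients, and the expectancy effect is expected to be weaker in those patients.

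**Controls.** Trial design {8}: "an age-, sex-, and education-matched control group of 30 participants will be recruited". Recruitment {15} repeats the same three factors: "The recruitment of the healthy control group is based on age, gender, and education of the patient group". Neither section mentions medication.

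**Patients.** Eligibility criteria {10} requires "at least two different antidepressants without sufficient effect in the patient history". The exclusion list removes neurological and cerebellar disease but names no drug class. Under concomitant care {11d}, "any existing drug and/or psychotherapeutic treatment is continued with as little change as possible".

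**Medication data and their use.** Confidentiality {27} states that "pre-existing conditions, previous treatments, and medications taken are recorded". The only stated analytic concern is a change of drugs: "Change of medication during the treatment is not an exclusion criterion per se but will be recorded as an event that will need additional control" (section {11b}, repeated in {11d}). Statistical methods {20a} plans repeated-measures ANOVA for the cerebellar tests, eyeblink conditioning included, and names no covariate. MRI group comparisons will include covariates that are not named.

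**The concern.** The comparison with healthy controls is not randomised, so its interpretation rests on the matching and the adjustment. Both omit the factor most likely to differ between patients from a treatment-resistant depression service and healthy volunteers: current psychotropic drugs. A drug that sedates or affects coordination could plausibly alter a reflex-learning task or resting-state connectivity without any contribution from depression.

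Two conclusions are exposed. One is the patient-control difference, which the protocol intends to describe as a change that goes with depressive illness. The other is the subset hypothesis. If patients fall into the impaired subset partly because of a drug, a weaker expectancy effect in that subset could follow the drug, or the reason it was prescribed, and not cerebellar function. The second conclusion is exposed even though it compares patients with patients.

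The provision on medication changes does not reach this problem. The Outcomes section places the cerebellar assessment at one time point before therapy, so what matters there is medication at baseline.

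**Working it through.** The protocol gives no sample size, power or effect size for this comparison, so there is no stated figure to reproduce. The calculation below is an illustration.

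**Inputs from the protocol.** 60 patients and 30 healthy controls (Eligibility criteria {10}).

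**Assumptions.**
- True effect of depression on the outcome: zero.
- Share p of patients on a relevant drug: 25%, 50% or 75%, that is 15, 30 or 45 of 60.
- Drug effect e: 0.5 or 0.8 SD in the direction of impairment.
- No control exposed.
- Two-sided t-test at 5%.

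**Step 1: mean shift.** The expected patient-control difference is p × e. At p = 0.50 and e = 0.8 it is 0.40 SD. At p = 0.25 and e = 0.5 it is 0.125 SD.

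**Step 2: standard error.** SE = √(1/60 + 1/30) = 0.224 SD.

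**Step 3: chance of a significant difference.** Simulated two-sample t-tests (100,000 trials per cell), with exactly p × 60 patients shifted by e:

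| Share exposed | Drug effect 0.5 SD | Drug effect 0.8 SD |
|---|---|---|
| 25% | 8% | 13% |
| 50% | 19% | 38% |
| 75% | 37% | 73% |

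With no drug effect the figure is 5%. A normal approximation with unit variance, Φ(p·e/SE − 1.96) + Φ(−p·e/SE − 1.96), gives slightly higher values (20% at 50% and 0.5 SD; 43% at 50% and 0.8 SD). It ignores the extra spread from mixing exposed and unexposed patients.

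**Step 4: what adjustment could do.** If no control takes such a drug, a model with diagnosis and a drug indicator estimates the diagnosis effect from unexposed patients against controls. Adding the covariate therefore uses the same information as restricting the patient group. Either way, the answer depends on how many patients are unexposed.

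**Step 5: precision of a restricted comparison.** SE = √(1/m + 1/30), with m patients remaining:
- m = 45: 0.236 SD, ratio to 0.224 = 1.05
- m = 30: 0.258 SD, ratio 1.15
- m = 15: 0.316 SD, ratio 1.41

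The effect detectable with 80% power is (1.96 + 0.84) × SE. It is 0.63 SD with all 60 patients and 0.89 SD with 15.

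**The case against.** **Covariates and sensitivity analyses are commonly left to the full protocol or analysis plan, and nothing here says medication will be ignored.** This stands in part. The unnamed MRI covariates may include medication, so the connectivity results cannot be called unadjusted. But the article itself fixes the contrast, the three matching factors, the rule on existing drugs and the intended interpretation, and these do not fit together. That goes beyond an unstated detail, most clearly for eyeblink conditioning.

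**Current medication is inferred.** This stands. Eligibility asks for failed antidepressants in the history, not current use, and the concomitant-care rule covers whatever treatment exists. No drug class is named, and the link from such drugs to the outcomes is an assumption. The low end of the illustration, 8%, is close to the nominal 5%.

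**Stronger readings that the documents do not support:**
- A reader might infer that drug exposure is almost completely confounded with diagnosis. The protocol does not state the share exposed. At the 25% to 75% assumed above, 45 to 15 patients are unexposed and carry usable information.
- A reader might infer that the cerebellar objective goes unanswered whichever way the test falls. The mechanism runs towards impairment, so it threatens a positive finding and gives no reason to distrust a null one.
- A reader might extend the point to a patient-control comparison of ataxia scores. The uses of the healthy group listed in Trial design {8} and at the end of the Outcomes section do not include ataxia scores or the neurological examination.

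**Drug use may track severity, so restricting or adjusting may remove true disease signal.** This stands, and it limits the form of the fix.

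**Conclusion.** The concern holds for the patient versus healthy-control comparison, chiefly of eyeblink conditioning, and for the impaired subset carried into the expectancy analysis. Followed as published, the plan could report a drug effect as a feature of depression. For connectivity the point is weaker, because unnamed covariates are planned.

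Its size cannot be read from the protocol. The 8% to 73% range rests wholly on the assumed share exposed and drug effect, on no exposure among controls and on no true effect of depression. It shows what could happen and does not estimate what will.

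The objectives affected are secondary. The randomised comparison of the two consent discussions is not confounded by baseline medication in this way.

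**What to change.** Before the data are analysed, and using the medication already recorded:

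1. Define a list of sedating or ataxia-producing drugs. As a sensitivity analysis, repeat the eyeblink and connectivity comparisons with only those patients taking none of them at the time of the assessment.
2. Report the impaired subset, and its relation to the expectancy effect, with and without adjustment for such medication.
3. Describe the main result as treatment-resistant MDD under existing medication versus healthy controls, unless it holds in the restricted comparison.

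No participant's treatment changes, and no recruitment or new measurement is needed. The cost is the loss of precision shown in the working, which is modest if most patients qualify and substantial if only 15 do. A restricted result that is merely non-significant should therefore not be read as showing a drug effect; report the estimate and its interval beside the full one. Because medication may track severity, the restricted and adjusted analyses should stand alongside the main comparison and not replace it.
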